## 2.3 Study Treatment Groups

There will be 3 parallel treatment groups:

- Sulphoraphane capsules 4.4 mg (25 micromoles) once daily by mouth
- Sulphoraphane capsules 26.6 mg (150 micromoles) once daily by mouth
- Matching Placebo (microcellulose) once daily by mouth

## 2.4 Eligibility Criteria

The entry criteria are designed to select patients who meet GOLD criteria for COPD who are likely to tolerate repeated bronchoscopies. Both active and former smokers will be enrolled because we are uncertain whether this will influence the outcome. Both active and former smokers show Nrf2 deficiency and in-vitro response to Nrf2 promoters. Patients are asked to limit intake of cruciferous vegetables (e.g. broccoli, cabbage, collard / mustard greens, kale, brussels sprouts, radishes) to no more than 1 serving per week to avoid confounding of results by dietary intake of sulforaphane.

#### **2.4.1 Inclusion Criteria:**

1. Age 40 or greater, either sex
2. 10 or more pack-years smoking history
3. Physician diagnosed COPD
4. Post bronchodilator FEV1/FVC ratio < 0.70
5. FEV1 40-80 % predicted
6. Willingness to ingest no more than 1 serving of cruciferous vegetables per week during run-in and treatment periods
7. Ability and willingness to provide informed consent

#### **2.4.2 Exclusion criteria:**

1. COPD exacerbation within preceding 6 weeks requiring treatment
2. Significant respiratory (other than COPD), cardiovascular, neuropsychiatric, renal, gastrointestinal, or genitourinary disease that would interfere with participation in the study or interpretation of the results.
3. Acute MI or Acute Coronary syndrome within 6 prior months
4. Cancer (other than skin or localized prostate) within preceding 5 years
5. Child-bearing potential with lack of adequate contraception, Pregnancy or lactation. Acceptable forms of birth control include abstinence, hysterectomy, tubal ligation, two of the following: vasectomy, condom, diaphragm, intrauterine device, oral or implanted contraceptives, or spermicide.
6. Allergy to local anesthesia
7. Resting hypoxemia ( $O_2$  saturation <90%)
8. Glomerular Filtration Rate (GFR) < 30 ml/min
9. Liver enzymes four times upper normal
10. Current use of warfarin for any indication

### **2.5 Outcomes**

Since this is a proof of principle study, we do not have a single primary outcome, but are evaluating several markers of Nrf2 activation and anti-oxidant activity. We will consider that we have established proof of principle if we can demonstrate an increase in Nrf2 expression and increased expression of at least two anti-oxidant enzymes.

#### **2.5.1 Primary outcome**

1. Nrf2 levels and downstream anti-oxidants The primary design variables are the change in Nrf2 expression in alveolar macrophages (AM) and bronchial epithelial cells (BEC). Support of antioxidant effects will be quantified by changes in phase II anti-oxidant gene expression (NQO1, HO-1, GPX2, GCLM, GCLC, GSTA1). We will correlate changes in these levels with non-invasive measures from peripheral blood monocytes and nasal epithelial cells.

#### **2.5.2 Secondary outcome**

Supportive secondary outcome measures will include measures of oxidant stress from plasma and expired breath condensate. We will also conduct ancillary exploratory studies to determine whether the treatment improves function of alveolar macrophages in bacterial clearance and improves steroid sensitivity. Markers of oxidative stress include 8-isoprostane,  $H_2O_2$ , GSH/GSSG, Nitrotyrosine, Protein carbonyls, TBARS

1. Measures of oxidative stress. Oxidant stress indicators (isoprostane) will be measured in plasma and expired breath
2. Measures of airway inflammation will be measured as BAL cell counts and cytokine profiles
3. Pulmonary function tests including spirometry will be measured to determine whether there are any short-term functional effects of the treatment.
4. Patient Reported Outcomes will include the MRC dyspnea scale and SGRQ which includes questions on cough and sputum production. Adverse events will include both spontaneous reports as well as targeted symptoms related to respiratory and GI systems. Adverse events will be scored based on the NCI Common Toxicity Criteria rating scale.
5. Safety Measures will include baseline (V1) and follow-up (V4) CBC and biochemical profile including renal function, thyroid function, and liver function tests. Women of childbearing potential will have a pregnancy test at V1 and V4.

## 2.6 Study Data Collection schedule

The specific study procedures and approximate time commitment from the participant are shown below:

Participants will have 5 study visits over 4-8 weeks as follows:

Visit 1 (V1) (Day – 28 to -7) (2 hours) During this visit, the participant will provide informed consent, undergo eligibility screening questionnaire, lung function (spirometry before and after bronchodilators), Complete Blood Count, biochemistry panel including renal and liver function and electrolytes, TSH, urinalysis, and a pregnancy test for women of child-bearing potential.

Visit 2 (V2) (Day -14 to 0) (2-4 hours) During this visit, eligible participants will perform baseline spirometry, lung volumes, and diffusing capacity, and will complete general health questionnaires and respiratory specific questionnaires (ATS-DLD, SGRQ and MRC). A brief physical examination will be performed. Baseline biological specimens including blood for PBMCs will be performed.

Visit 3 (V3) (Day 0) (4 hours) The participant will have a baseline bronchoscopy for collection of bronchoalveolar lavage cells and nasal and bronchial epithelial brushings. Randomization eligibility will be established and the participant will be assigned to a masked treatment. After recovery from the bronchoscopy sedation, the participant will be given the assigned treatment which will consist of a coded container of capsules containing either placebo or one of the two doses of sulforaphane.

Phone Visit 1 (P1) (Day 1) (15-30 minutes) Patients are phoned the day following the bronchoscopy to determine whether they have had any adverse experiences, to re-instruct them in use of the medication, and to confirm future appointment dates and times.

Phone Visit 2 (P2) (Day 7-14) (15-30 minutes) Patients are contacted to determine their compliance with the medication and to report any adverse effects.

Visit 4 (V4) (Day 21 to 30) (2 – 4 hours) The participant will repeat the baseline spirometry, lung volumes and diffusion capacity, CBC, pregnancy test, urinalysis, TSH and biochemistry panel and have follow-up health status and adverse effect questionnaires and a brief physical examination. Follow-up collections of blood for biological measures are obtained.

Visit 5 (V5) (Day 22 to 31) (4 hours) Follow-up bronchoscopy for collection of bronchoalveolar lavage, nasal brushings, specimens and endobronchial brushings. Return of unused capsules for pill counts.

Phone Visit 3 (P3) (Day 24 to 38) (15-30 minutes) Exit interview and followup for adverse effects of bronchoscopy.

**Table 1: Study Data Collection Schedule**

| Visit                           | V1        | V2       | V3 | P1 | P2   | V4    | V5    | P3    |
|---------------------------------|-----------|----------|----|----|------|-------|-------|-------|
| Time window (days)              | -28 to -7 | -14 to 0 | 0  | 1  | 7-14 | 21-30 | 22-31 | 24-38 |
| Target (days)                   | -21       | -14      | 0  | 1  | 14   | 25    | 26    | 27    |
| Consent, eligibility evaluation | •         |          |    |    |      |       |       |       |
| Screening Questionnaire         | •         |          |    |    |      |       |       |       |
| Spirometry/PFTs                 | •         | •        |    |    |      | •     |       |       |
| Pulse Oximetry                  | •         | •        |    |    |      |       |       |       |
| Lung volume/DCO                 |           | •        |    |    |      | •     |       |       |
| CBC, Chemistry panel, TSH       | •         |          |    |    |      | •     |       |       |
| Urine analysis                  | •         |          |    |    |      | •     |       |       |
| Physical Exam                   |           | •        |    |    |      | •     |       |       |
| Pregnancy Test                  | •         |          |    |    |      | •     |       |       |
| Randomization                   |           |          | •  |    |      |       |       |       |
| Health Status / AE              |           | •        |    |    |      | •     |       |       |
| SGRQ/MRC                        |           | •        |    |    |      | •     |       |       |
| ATS-DLD                         |           | •        |    |    |      |       |       |       |
| EBC                             |           | •        |    |    |      | •     |       |       |
| PBMC/Plasma/Serum               |           | •        |    |    |      | •     |       |       |
| Nasal Brush                     |           |          | •  |    |      |       | •     |       |
| BAL/Bronchial Brush             |           |          | •  |    |      |       | •     |       |
| Adherence Counseling            |           |          |    | •  | •    |       |       |       |
| Exit interview                  |           |          |    |    |      |       |       | •     |

KEY: AE = adverse event questionnaire, ATS-DLD = ATS-DLD respiratory questionnaire, BAL = Bronchoalveolar lavage, CBC = complete blood count, DCO= Diffusion capacity for carbon monoxide, EBC = Expired Breath Condensate, MRC = Medical Research Council Dyspnea Scale, PBMC = Peripheral Blood Monocyte Collection, SGRQ = St George's Respiratory Questionnaire, TSH = Thyroid Stimulating Hormone, UA = Urinalysis

## 2.7 Study Procedures

A variety of biological samples will be collected from patients with COPD for analysis of Nrf2 activity and related phase II enzymes.

### **2.7.1 Biospecimens**

Bronchoalveolar lavage (BAL). Patients, fasting for 6 hours prior to the procedure, are sedated with midazolam and fentanyl. The bronchoscope is introduced via the nares into the trachea under local anesthesia with 1% or 2% lidocaine. The bronchoscope is wedged into two subsegments of the right lung (anterior segment of upper lobe, and lateral segment of middle lobe). In each subsegment 3 x 50 ml aliquots of normal saline are instilled and withdrawn. The lavage material, which averages 25% return in patients with COPD contains typically yields  $1-10 \times 10^6$  macrophages which are sufficient for all of the assays proposed in this study. The centrifuged cell pellet is divided into two aliquots and one aliquot is stored at -70C. The supernatant is divided into 4-5 aliquots and stored in cryotubes.

Bronchial brushings. Prior to the bronchoalveolar lavage, a cytology brush is inserted into the bronchoscope channel and brushings are collected from 4 quadrants of visible subsegments of the right lung under direct visualization. The cellular material is washed off in saline and the procedure is repeated 10 times. The liquid is centrifuged and the cell pellet is stored at -70C.

Nasal brushings. Each nostril is anesthetized with lidocaine 1% spray. A nasal cytology brush is gently rubbed along the lower turbinate and rinsed in normal saline. The procedure is repeated three times in each nostril. The centrifuged cell pellet is stored at -70C.

Peripheral Blood Monocytes Collection (PBMC). 60 ml of blood is withdrawn by venipuncture and the buffy coat is separated. Monocytes are separated in a Ficoll-Hypaque gradient, washed and frozen at -70C.

Plasma. Plasma from the blood collection is prepared by centrifugation and stored at -70C. This plasma will be held for exploratory supplementary measures of cytokines that are not included in this application.

Expired Breath Condensate (EBC) is collected using the R-tube method in which a refrigerated aluminum tube is placed over a disposable valved collecting tube and condensate trap. After 5-10 minutes of quiet tidal breathing, approximately 0.5-1.0 ml of condensate is collected and frozen at -70C pending measurement of isoprostane.

Blood draw 10-20 ml of blood is collected by venipuncture at V1 and V4 for complete blood count and biochemistry profile (comprehensive metabolic panel). These tubes are transmitted to the local hospital laboratory without processing.

Urine. A spot sample of urine will be collected and analyzed for routine urinalysis in the local hospital laboratory

**Table 2: Biological measures to be assessed in different biological samples**

| Procedure                                  | Biological sample          | Biological measures*                            |
|--------------------------------------------|----------------------------|-------------------------------------------------|
| Exhaled breath condensate (EBC) collection | EBC                        | Oxidative stress markers*                       |
| Blood collection                           | PBMC                       | Nrf2 activity**                                 |
|                                            | Plasma                     | Oxidative stress markers                        |
| Nasal brushing                             | Nasal epithelial cells     | Nrf2 activity                                   |
| Bronchoscopy                               |                            |                                                 |
| • Bronchial brushings                      | Bronchial epithelial cells | Nrf2 activity, oxidative stress markers         |
| • Bronchoalveolar lavage (BAL)             | Alveolar macrophages       | Nrf2 activity, inflammatory cytokines***, NF-KB |
|                                            | BAL fluid                  | Inflammatory cytokines                          |

\*Oxidative stress markers include Isoprostane and, in fresh specimens H2O2.

\*\*Nrf2 activity: Nrf2 activity will be assessed by measuring: 1) Nrf2 protein, 2) expression of a panel of Nrf2 regulated genes (antioxidants and proteasomal subunits) 3) GSH levels and 4) Proteasomal activity.

\*\*\*Cytokine assays include IL6, IL8, TNF-alpha, INF-gamma, and MIP.

## 2.7.2 Physiologic measures

### Spirometry

Spirometry will be performed at V1, V2, and V4 in accordance with ATS/ERS recommendations. Spirometry reference values will be those of Hankinson et al from NHANES. At V2, and V4 participants will also have lung volume measurements and diffusing capacity measurements performed for the purpose of characterization and to exclude patients with restrictive lung disease. These measures will be performed in accordance with local hospital laboratory procedures.

## 2.7.3 Patient reported outcomes

### Questionnaires

ATS-DLD respiratory questionnaire as modified for use in the Lung Tissue Research Consortium (LTRC) will be completed at V2. This instrument is used to define respiratory exposures to cigarettes and other occupational / environmental agents as well as to describe severity and frequency of respiratory symptoms such as cough, phlegm, and dyspnea.

St. George's Respiratory Questionnaire (SGRQ) will be completed at V2 and V4. This is a validated self-completed questionnaire that assesses respiratory-specific quality of life and disease impact with 3 domains and an overall score. We are not expecting to find significant short-term changes in SGRQ with sulforaphane treatment, however we are using this instrument to characterize the disease severity of our treatment population and acquire measures of short-term intra-individual variability that will assist us with planning of future trials should this approach be used in the future.

Medical Research Council (MRC) dyspnea scale will be completed at V2 and V4 to categorize the extent of activity limitation due to dyspnea on a 5 point scale.

Health Status and Adverse Event questionnaires will be completed at V2, P2, and V4 to ascertain whether there have been any significant illnesses, interval illnesses or changes in treatment, or new symptoms reflecting adverse events. Typically targeted adverse events are asked about specifically, and other adverse events are solicited by open-ended questioning and categorized as mild, moderate or severe using standard definitions. Because sulforaphane has such a clean profile with respect to adverse events, we are not planning to ask about specific targeted sulforaphane events, but we will ask about interval respiratory infections or exacerbations as well as specific symptoms related to the bronchoscopy procedures.

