### **1.5 Objectives**

The primary goals of this trial are to:

- Establish proof of principle -- Does oral sulforaphane increase Nrf2 expression and downstream anti-oxidant enzymes in lung macrophages and epithelial cells.
- Determine tolerability and dose-ranging for subsequent clinical research
- Establish non-invasive surrogate biomarkers for Nrf2 expression in the lung
- Conduct ancillary mechanistic studies to determine whether *in-vivo* treatment increases bacterial phagocytosis and killing and decreases corticosteroid resistance

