### **3.4 Unmasking**

Drug and placebo will be supplied in similar appearing capsules, back-filled with methylcellulose to approximate similar appearance and weight. Neither the participant nor the site investigators or the laboratory personnel will know the identity of the drug assignment. Emergency unmasking can take place by opening a sealed envelope that is distributed with the drugs. All unmasking events are reported to the DCC. The sealed envelopes are returned to the DCC at the end of the trial. Also, the investigators doing the bioassays will do them masked to treatment assignment. It is our general position that unmasking of treatment assignment is rarely necessary. If adverse events occur that may be related to the study treatment, then the study treatment is stopped and the patient is followed on an intention to treat basis. Envelopes with treatment assignment are provided to the clinic in the case a treating physician feels it is important to know the treatment assignment.

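### Protocol sections 2.5.2 and 2.7.3 disagree on whether GI symptoms are asked about, and Table 1 omits one scheduled adverse-event questionnaire, although tolerability is a primary goal

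*Protocol*

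**What the plan says.** Section 1.5 lists among the primary goals: "Determine tolerability and dose-ranging for subsequent clinical research". Section 2.2 also gives the assessment of tolerability as one reason for the four-week treatment period.

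Two sections then describe how adverse events are collected.

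- Section 2.5.2, item 4: "Adverse events will include both spontaneous reports as well as targeted symptoms related to respiratory and GI systems". On grading: "Adverse events will be scored based on the NCI Common Toxicity Criteria rating scale".
- Section 2.7.3, Questionnaires: because of the compound's favourable record, "we are not planning to ask about specific targeted sulforaphane events". The specific questions that remain are these: "we will ask about interval respiratory infections or exacerbations as well as specific symptoms related to the bronchoscopy procedures". Other events are left to open-ended questioning and, in a sentence about usual practice, are "categorized as mild, moderate or severe using standard definitions".

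On timing, section 2.7.3 states: "Health Status and Adverse Event questionnaires will be completed at V2, P2, and V4". The Health Status / AE row of Table 1 is marked at V2 and V4 only. P2 is marked in that table only for adherence counseling.

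**The concern.** Prompted and open-ended questioning generally yield different event counts, so whether GI symptoms are on the form is a measurement decision. For a daily oral capsule, GI is also the one targeted domain in section 2.5.2 that section 2.7.3 does not cover through its respiratory and bronchoscopy questions.

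The reason section 2.7.3 gives for dropping targeted questions is that the compound is already known to be well tolerated. That presumes part of what the trial sets out to establish at two doses.

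At stake is the evidence for the tolerability and dose-ranging goal. What is asked, when, and on which scale belongs to the protocol and its forms. An analysis plan cannot recover symptoms that nobody asked about.

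**Working it through.** The documents state no adverse-event rate, tolerability threshold or sample size for tolerability, so there is no figure to reproduce on this point. The check compares the texts. An illustration on assumed rates follows.

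**1. The texts side by side**

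| Item | Section 2.5.2 | Section 2.7.3 | Table 1 |
|---|---|---|---|
| Respiratory symptoms | targeted | specific questions kept | – |
| Bronchoscopy symptoms | not named | specific questions kept | – |
| GI symptoms | targeted | not named; targeted sulforaphane events declined | – |
| Grading | NCI criteria | mild/moderate/severe, as usual practice | – |
| Questionnaire timing | not given | V2, P2, V4 | V2, V4 |

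- *GI symptoms:* a direct conflict. One section targets them; the other leaves them to the open question.
- *Respiratory symptoms:* no real conflict.
- *Grading:* a missing link. Three severity labels could be mapped to NCI grades, but no mapping is given.
- *Timing:* one cell conflicts, P2.

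**2. What the P2 cell carries**

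V2 precedes treatment, which is dispensed at V3 (day 0). Table 1 gives target days of 14 for P2 and 25 for V4. With the P2 form, the two on-treatment recall periods are 14 days and 25 − 14 = 11 days. Without it there is a single period of 25 days. P2 is the only scheduled on-treatment questionnaire before V4.

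**3. Illustration of under-capture (all rates assumed)**

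Let p0 and p1 be the true proportions with GI symptoms on placebo and on an active dose, and c the fraction recorded, equal in all arms. The observed difference is c × (p1 − p0). The ratio of proportions is unchanged, but the difference and the counts shrink by the factor c.

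With p1 = 30%, p0 = 10% and 30 patients per arm (section 4.1):

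- c = 1: 30% − 10% = 20 points; 9 − 3 = 6 patients.
- c = 1/2: 15% − 5% = 10 points; 4.5 − 1.5 = 3 patients.
- c = 1/3: 10% − 3.3% = 6.7 points; 3 − 1 = 2 patients.

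Power of a two-sided Fisher exact test at 0.05, 30 against 30, is the sum, over all pairs of counts with p ≤ 0.05, of Bin(i; 30, c·p1) × Bin(j; 30, c·p0):

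| Assumed true rates (p0 vs p1) | c = 1 | c = 0.75 | c = 0.5 | c = 0.25 |
|---|---|---|---|---|
| 5% vs 30% | 63% | 41% | 16% | 2% |
| 10% vs 30% | 37% | 23% | 9% | 1% |
| 10% vs 40% | 71% | 49% | 24% | 4% |

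The protocol does not propose this test for adverse events. The table shows only how visible a GI difference would be at this arm size.

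**The case against.** There is a good deal to say on the other side, and most of it limits the point without removing it.

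- **Section 2.7.3 does not abandon targeted questions.** It keeps the respiratory and bronchoscopy questions. A reader might infer that nothing is prompted, but the text does not support that. The conflict is about GI symptoms.
- **The grading texts need not be rival scales.** The mild/moderate/severe wording describes what is typically done and names no competing standard. A reader might infer two incompatible scales; only an unstated link is shown.
- **The other phone calls do not conflict.** P1 is a day-after call, and P3 is an exit interview with bronchoscopy follow-up. Neither is said to use this questionnaire, so neither contradicts its schedule. Section 2.6 also has adverse effects reported at P2, so P2 would not be silent even without the form.
- **The arms stay comparable within a site.** Section 3.4 states: "Neither the participant nor the site investigators or the laboratory personnel will know the identity of the drug assignment". A reader might infer that the two sections make the arms non-comparable, but masked staff would question all arms alike. Differences could arise between the three sites, or over time, if staff followed different sections. Section 4.5 requires training, certification and a knowledge assessment, which makes that less likely. Training on a protocol that contradicts itself does not settle which section applies.
- **Tolerability has other evidence.** There are pill counts at V5, laboratory tests at V1 and V4, the open question, and safety board review of serious events, defined to include permanent discontinuation of treatment. Severe GI intolerance would probably surface. Milder symptoms are where prompting matters most.
- **The main outcome is untouched.** The proof-of-principle criterion in section 2.5 is Nrf2 and antioxidant expression, and adverse events are listed under secondary outcomes. Section 1.5 nonetheless makes tolerability a primary goal.

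Masking does not answer the under-capture concern. A capture fraction that is equal in all arms still shrinks a true difference.

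**Conclusion.** The contradiction on GI symptoms is real, stands in the current text and bears on a stated primary goal. The omitted P2 mark and the unlinked severity wording are smaller inconsistencies in the same instrument.

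The consequence is conditional. If section 2.7.3 is followed, GI intolerance could be under-captured in all arms and a true dose difference would appear smaller. If sites follow different sections, their event rates could differ. Neither outcome is certain, and the documents do not say which section would prevail.

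The size cannot be derived from the documents. The fall from 6 to 2–3 excess patients in 30, and the power figures above, rest wholly on assumed event rates and capture fractions, and on a GI excess existing at all. They show that ascertainment could matter at this arm size, not that it would.

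**What to change.** Reconcile the sections before data collection:

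1. Use the targeted respiratory and GI list of section 2.5.2 plus an open question, on the same form, at V2, P2 and V4. Keep the bronchoscopy questions.
2. Delete or amend the sentence in section 2.7.3 that declines targeted sulforaphane events.
3. Name the NCI criteria in section 2.7.3 as the grading scale, or state how the three severity labels map to NCI grades.
4. Mark P2 in the Health Status / AE row of Table 1.

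The full form is not needed at P1 or P3 to remove the contradiction.

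The cost is a protocol amendment and one revised form, used at visits and a call that already exist. The downside is a few extra minutes per contact and more low-grade events on record.

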### **3. Study Treatments**

#### **3.1 Assigned treatments**

1. 25 micromoles (4.4 mg) sulforaphane once daily by mouth
2. 150 micromoles (26.6 mg) sulforaphane once daily by mouth
3. Placebo (microcellulose) once daily by mouth

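### Section 2.5.2 counts targeted GI symptoms as adverse events, but section 2.7.3 rules out targeted sulforaphane questions and lists no GI item, so GI tolerability of an oral product may be under-recorded

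*Protocol*

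**What the plan says.** Protocol section 1.5 lists this among the primary goals: "Determine tolerability and dose-ranging for subsequent clinical research". Treatment is oral in all three arms; the high-dose arm in section 3.1 is "150 micromoles (26.6 mg) sulforaphane once daily by mouth".

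Two sections describe how adverse events are collected.

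- Section 2.5.2, in the item on patient reported outcomes: "Adverse events will include both spontaneous reports as well as targeted symptoms related to respiratory and GI systems". The next sentence sets the grading: "Adverse events will be scored based on the NCI Common Toxicity Criteria rating scale".
- Section 2.7.3, on the Health Status and Adverse Event questionnaires: "we are not planning to ask about specific targeted sulforaphane events". The reason given is that sulforaphane has a favourable adverse event profile. The directed questions that remain are set out as "we will ask about interval respiratory infections or exacerbations as well as specific symptoms related to the bronchoscopy procedures". The preceding sentence, which describes what is typically done, says that "other adverse events are solicited by open-ended questioning" and that events are "categorized as mild, moderate or severe using standard definitions".

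Table 1 shows only a line for health status and adverse events and does not say what the form contains.

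**The concern.** The outcome section promises directed GI questions and the procedures section does not provide for them. For a product taken by mouth, GI symptoms are an obvious candidate for a treatment effect, and GI is one of only two body systems that 2.5.2 singles out. The reason given in 2.7.3 for not asking presumes part of the answer that the tolerability goal is meant to supply.

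What is at stake is data collection rather than analysis. A symptom that was never asked about and never volunteered cannot be recovered by any analysis plan after the four-week course. Patients tend to volunteer fewer mild symptoms than they confirm when asked by name. Open questioning alone would therefore probably lower the recorded GI rate in all arms, and with it the absolute difference between each dose and placebo. A dose could then look better tolerated than it is. Section 2.2 justifies the four-week treatment period partly by the need to assess tolerability, and the abstract states the aim of finding a safe and tolerable dose, so the point bears on a declared purpose of the trial.

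**Working it through.** **Step 1: compare the two sections.** The plan states no figure on this point, so the main check is textual.

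| Item | Section 2.5.2 | Section 2.7.3 | Consistent? |
|---|---|---|---|
| GI symptoms | Targeted | No GI item among the directed questions; targeted sulforaphane questions ruled out | No |
| Respiratory symptoms | Targeted | Infections, exacerbations and bronchoscopy symptoms still asked about | Largely |
| Unprompted events | Spontaneous reports | Open-ended questions | Yes |
| Severity | NCI criteria | Mild, moderate or severe by unnamed standard definitions | Reconcilable, but no mapping stated |

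The GI row cannot be rescued by treating GI symptoms as something other than sulforaphane events, because they are also absent from the items that 2.7.3 keeps. The clear conflict is confined to that row.

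**Step 2: direction of the effect if 2.7.3 governs.** Let p_H and p_P be the true GI rates at the high dose and on placebo, and c the fraction of true cases that open questioning records, taken as equal in the arms. The recorded difference is c·p_H − c·p_P = c(p_H − p_P). Any c below 1 shrinks it, whatever the true rates are.

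**Step 3: size, as an illustration only.** The group size of 30 comes from section 4.1. The GI rates, the capture fractions and the threshold of 4 cases are assumptions.

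*(a) Cases seen in one arm.* With a true rate of 20%, the recorded number X follows a Binomial(30, 0.20c) distribution.

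| c | Expected cases (30 × 0.20 × c) | P(X ≥ 4) |
|---|---|---|
| 1.0 | 6.0 | 0.877 |
| 0.5 | 3.0 | 0.353 |
| 0.4 | 2.4 | 0.216 |

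*(b) Comparison of high dose and placebo.* Power of the two-sided Fisher exact test at 0.05, with 30 per arm:

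| True rates | Full capture | Half capture |
|---|---|---|
| 40% vs 10% | 0.705 | 0.241 (20% vs 5% recorded) |
| 20% vs 10% | about 0.10 | about 0.02 (10% vs 5% recorded) |

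The first row shows a large loss. The second shows that with a modest true effect the trial could hardly separate the arms even if every case were recorded. The loss therefore depends heavily on rates that the documents do not give.

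**The case against.** The strongest case on the other side has five parts.

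1. **GI symptoms are not excluded.** A reader might infer that nobody would be asked about them. The text does not support that. Section 2.7.3 rules out only specific targeted questions and keeps enquiry about new symptoms at V2, P2 and V4, and section 2.6 has patients report adverse effects at P2. This stands: GI symptoms go unnamed, not unasked.
2. **The respiratory half is not in conflict.** Directed questions on infections and exacerbations remain, and the SGRQ and MRC scale cover respiratory symptoms. This stands.
3. **The grading wording is compatible.** A reader might infer two rival scales that would prevent a single severity table by dose. The three-level wording sits in a sentence about typical practice, names no competing scale, and can be mapped to NCI grades. This stands, and leaves only a clarification to make.
4. **Under-counting is not certain.** It follows only if the form was built from 2.7.3. The protocol does not say so and the form is not reproduced in it. If the form follows 2.5.2, nothing is lost. This stands as a condition. However, 2.7.3 is the section that describes the questionnaire, and with three clinical sites (section 4.4) an unresolved conflict is itself a risk.
5. **No GI comparison is powered.** Section 4.1 powers only Nrf2 and antioxidant analytes, and adverse events are listed among the secondary outcomes. Laboratory safety tests are unaffected, and events requiring permanent discontinuation still reach the DSMB under section 4.3. This limits the consequence. But laboratory tests would not detect symptoms such as nausea, and milder intolerance would not appear as a discontinuation.

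Open questioning alone could also be a legitimate design choice. The error is that the protocol commits to both methods.

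**Conclusion.** The contradiction over GI symptoms is real and nothing else in the protocol resolves it. If 2.7.3 governs, GI tolerability would probably be under-recorded in all arms and any dose difference would look smaller. That conclusion assumes that open questions catch fewer GI symptoms than named ones, at a similar fraction in each arm. The size cannot be derived from the documents, so the figures above show only that the loss could range from large to immaterial, depending on the true rates.

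This is a point that should be fixed, not one on which the trial depends. It bears on a stated primary goal, tolerability and dose-ranging, but leaves the Nrf2 and antioxidant outcomes and their analysis untouched.

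**What to change.** Reconcile section 2.7.3 with section 2.5.2:

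- Remove the statement in 2.7.3 that targeted sulforaphane events will not be asked about.
- Put the targeted GI symptom items promised in 2.5.2 into the adverse event questionnaire at baseline and at each later administration, next to the open-ended question and identically in all arms. Section 2.7.3 lists V2, P2 and V4, while Table 1 marks only V2 and V4; settle that list in the same edit.
- As a minor clarification, state in 2.7.3 that the mild, moderate and severe categories are graded by the NCI criteria named in 2.5.2.

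The cost is a few lines on the form and a short wording change. The downside is that more mild symptoms will be recorded in every arm, placebo included. Asking the same items at baseline helps to separate pre-existing complaints from new ones.
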